## Abstract

**Introduction:**

Around 25% of patients with bladder cancer (BCa) present with invasive disease. Non-randomised studies of population-based screening have suggested reductions in BCa-specific mortality are possible through earlier detection. The low prevalence of lethal disease in the general population means screening is not cost-effective and there is no consensus on the best strategy. Yorkshire has some of the highest mortality rates from BCa in England. We aim to test whether population screening in a region of high mortality risk will lead to a downward stage-migration of aggressive BCa, improved survival and is cost-effective.

**Methods and analysis:**

YORKSURe is a tiered, randomised, multicohort study to test the feasibility of a large BCa screening randomised controlled trial. In three parallel cohorts, participants will self-test urine (at home) up to six times. Results are submitted via a mobile app or freephone. Those with a positive result will be invited for further investigation at community-based early detection clinics or within usual National Health Service (NHS) pathways. In Cohort 1, we will post self-testing kits to research engaged participants (n=2000) embedded within the Yorkshire Lung Screening Trial. In Cohort 2, we will post self-testing kits to 3000 invitees. Cohort 2 participants will be randomised between haematuria and glycosuria testing using a reveal/conceal design. In Cohort 3, we will post self-testing kits to 500 patients within the NHS pathway for investigation of haematuria. Our primary outcomes are rates of recruitment and randomisation, rates of positive test and acceptability of the design. The study is currently recruiting and scheduled to finish in June 2023.

**Ethics and dissemination:**

The study has received the following approvals: London Riverside Research Ethics Committee (22/LO/0018) and Health Research Authority Confidentiality Advisory Group (20/CAG/0009). Results will be made available to providers and researchers via publicly accessible scientific journals.

**Trial registration number:**

ISRCTN34273159.

STRENGTHS AND LIMITATIONS OF THIS STUDYThe multicohort approach allows for contemporaneous assessment of each facet of the study while permitting the participant pathway to be dynamically optimised.The conceal/reveal design offers high compliance and low contamination, but may be concerning to participants.Organisational logistics to implement such a study design is exhaustive and relies on collaboration with several industry vendors.The acceptability and usability of the study platforms are uncertain.The sensitivity of a diagnostic pathway without initial flexible cystoscopy is unknown.

## Introduction

Bladder cancer (BCa) is a common malignancy and one of the most expensive to manage.^1 2^ BCas are best stratified into non-muscle-invasive (NMI) and muscle invasive (MI) cancers. In the UK, around 25% of patients present with MI BCa which requires radical treatment in an attempt at cure.^3 4^ BCa rates increase with age, smoking and occupational carcinogen exposure.^5–7^ Consequently, BCa incidence and mortality demographics often match local risk factor patterns of exposure. Yorkshire has some of the highest incidence and mortality rates of BCa in England, perhaps reflecting lifestyle choices and local industries.^2 8–10^

In contrast to many human malignancies, disease-specific survival for BCa is not improving,^2 11^ suggesting a need to change the approach to manage this cancer. Many BCa’s present late to healthcare professionals as the symptoms mirror those of common benign conditions, such as bacterial cystitis, detrusor overactivity or prostatic enlargement.^12^ Within the NHS, more BCas are diagnosed following routine General practitioner (GP) referral (41.3% (CI: 40.7% to 42.0%)) for urinary symptoms than via 2 week-wait (2ww) pathways (27.5% (CI: 26.9% to 28.1%)), and the rate of emergency presentation increases with advancing tumour stage, from 6.4% for NMI to 18.8% for MI BCas.^2^

### Current knowledge: BCa early detection

Most BCas are diagnosed in persons with visible haematuria (VH) or non-visible haematuria (NVH).^13^ As such, there is potential to use haematuria to detect asymptomatic disease earlier than would occur otherwise.^14^ Indeed, patient surveys reveal many individuals complain of irritative bladder symptoms (dysuria, frequency) prior to developing VH.^15 16^ However, there have been few attempts at screening for BCa using haematuria. Two non-randomised single arm studies found that haematuria testing in asymptomatic persons leads to earlier stage of cancers at detection and may improve survival.^17 18^ Britton *et al* screened 2356 British men and found 17 BCas, of which all were NMI.^19^ At 7 years, 33% of the high-grade NMI cohort had died from BCa, reflecting potential undermanagement of this aggressive cancer.^20^ Messing *et al* screened 1575 American men and found a lower stage at diagnosis, with reduced BCa mortality rate (0%) in screened men compared with rates in men from a matching state-wide registry (16.4% mortality rate).^18^ The authors concluded that screening did reduce mortality, but it needs to be applied in high-risk populations and that haematuria is intermittent in patients with BCa.^21^ In populations exposed to aristolochic acid, Zlotta *et al* found survival (0% mortality) occurred only with screening (100% mortality in non-screened patients),^22^ supporting the potential for BCa screening to be cost-effective in high-risk populations.^23^

### Research need

YORKSURe is a feasibility trial aimed at the early diagnosis of BCa through the detection of haematuria in asymptomatic individuals at high risk of mortality from the cancer. Following results of the feasibility trial, the aim is to conduct a large-scale trial, with sufficient power to test any differences in BCa mortality. However, to undertake this successfully, we need to understand if our proposed approach is robust, appropriate, necessary and acceptable to participants. Here we detail the trail using Protocol V.5.0 date 16 January 2023.

#### Study aims and objectives

Three cohorts will be studied in this feasibility study. Each will address a separate aim, all of which are needed to develop a phase III prospective trial:

Aim 1: Cohort 1 will test compliance, prevalence of haematuria and BCa and the economics of the trial within a screening-engaged population. It might suggest that BCa screening works best when embedded within lung screening services. It will also test women and populations younger than typical for the highest risk BCa age group.Aim 2: Cohort 2 will test compliance, prevalence of haematuria and BCa, prevalence of glycosuria and undiagnosed diabetes within a high-risk community-based population.Aim 3: Cohort 3 will provide a positive predictive value (PPV) of the study tests (urine self-testing, urine cytology and ultrasound) as assessed in a population already referred in the NHS 2ww haematuria pathway.

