### Investigation of haematuria

Participants in Cohort 1 and those randomised to the haematuria arm of Cohort 2 will be investigated for the presence of haematuria (figures 1 and 2). If a single positive result is identified on research nurse review of the erythrocyte test parameter, then the participant will be invited to attend an Early Detection Clinic (run in a nearby GP surgery and staffed by study-employed or NIHR Clinical Research Network (CRN)-employed nursing staff) within 4–6 weeks of assessment of their results. At this clinic, participants will undergo a urinary tract ultrasound scan (USS) and provide a urine sample for cytology. Those with an abnormal USS (bladder or renal mass suggestive of cancer detected) or abnormal cytology will be referred by their GP or the research nurse team (following standard NHS 2ww criteria) to their local urology haematuria service for evaluation (flexible cystoscopy and additional assessments). We expect that around 20% of participants with self-testing haematuria will require referral. The test results for these participants will be obtained directly through the relevant urology departments and categorised into: BCa diagnosis, kidney cancer diagnosis, upper tract urothelial cancer diagnosis, urinary stones, infection or inflammation, stricture, clinically benign prostatic enlargement, post-TURP (transurethral resection of the prostate), diagnosis unclear/further tests planned, likely prostate cancer, no abnormal finding or other finding. Participants with normal USS and normal cytology, from the early detection clinic, will receive a letter explaining this and discharging them from the study. They will receive advice about the need to see their GP if they have urinary symptoms or VH. Their GP will receive a letter with advice about management of NVH. Participants without haematuria will receive a letter confirming their result and informed that their GP will also be notified of their results. They will be asked to seek a GP appointment if they develop urinary symptoms in the future. Participants in cohort 3 will undergo standard NHS assessment of haematuria as part of their referral process (regardless of their test strip results). This includes cystoscopy and upper tract imaging (typically CT urogram and USS).

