### Investigation of glycosuria

Participants randomised to the glycosuria arm of Cohort 2 will be investigated for the presence of glycosuria. Glycosuria was chosen as it is a validated urine test that can detect a meaningful disease (diabetes mellitus), whose outcomes are better detected at an early stage. If a single positive result is identified on research nurse review of the glucose test parameter, then the participant will be invited to attend an Early Detection Clinic within 4–6 weeks of assessment of their results. At the clinic, participants will undergo hemoglobin A1c (HbA1c) blood testing. Those with elevated HbA1c (as defined by local reference ranges) will be referred to their GP for diabetic management. Those with a normal HbA1c (as defined by local reference ranges) will receive a letter explaining that their test was normal and will be advised to see their GP if they think they have diabetic symptoms. Their GP will also be informed of the test result. Participants in the glucosuria testing arm without glycosuria will receive a letter confirming their normal result and informed that their GP will also be notified of their results. Participants will be advised to seek a GP appointment if they develop diabetic symptoms.

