### Primary outcomes

This is a feasibility study and so there are multiple primary outcomes reflecting each stage of the study and what we need to understand for a larger phase III randomised controlled trial:

1. Acceptability of urine self-testing and the Early Detection Clinics will be measured by:

1.1. Proportion of invitees who report results for at least one test strip.

1.2. Proportion of participants who attend and consent for cytology and urinary tract ultrasound following detection of haematuria on self-testing.

1.3. Proportion of participants who attend and consent for HbA1c blood testing following the detection of glycosuria on self-testing.

2. Compliance with urine self-testing will be measured by;

2.1. The proportion of participants who report results for (i) all six test strips and (ii) three or more test strips.

2.2. The number of test strips returned on average in those who return at least one test strip.

3. Prevalence of haematuria will be measured from the proportions of participants with ≥1 test strip positive for haematuria.

4. Prevalence of glycosuria will be measured from the proportions of participants with ≥1 test strip positive for glycosuria.

5. Haematuria clinic outcomes will be measured via:

5.1. The proportion of participants with a positive or abnormal cytology in those where a urine sample is collected.

5.2. The proportion of participants who have an abnormal USS, who underwent scanning.

6. Glycosuria clinic outcomes will be measured via the proportions of those with an elevated HbA1c following collection of a blood sample.

7. Urinary symptoms will be measured via symptom scores from the urine symptoms questionnaire (as completed prior to self-testing).

8. BCa in the tested population will be measured via the proportions of BCa cases and corresponding stage in identified participants (excluding non-responders and withdrawals).

9. The accuracy of self-testing, cytology and USS will be measured via:

9.1. The sensitivity, specificity, PPV and negative predictive value (NPV) of the following in men and women with cancer as identified by cystoscopy results at the 2ww appointment

9.1.1. Self-testing (App vs freephone).

9.1.2. Cytology and ultrasound (separately and in combination) as a triage test in those with positive haematuria

9.2. The predictive value of symptoms in combination with self-testing:

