### Data collection

Self-test results and questionnaire data will be captured in the bespoke mobile app and freephone system. The questionnaire will collect information on diabetes (diagnosis and management), smoking status, ethnic group, lesbian, gay, bisexual, and transgender (LGBT) identification, highest level of education, history of factory work as well as bladder symptoms (via a modified and unvalidated version of the UTISA Questionnaire^25^). Cohort 1 and 2 data collected at Early Detection Clinics will be entered into a REDCap^26^ database and will include height and weight, current occupation, previous longest occupation, concomitant medication, ultrasound results, urine cytology results and HbA1c results. Data for Cohort 1 and 2 participants who are subsequently referred for a 2ww, and consenting Cohort 3 participants, will be obtained via medical records to include results of cystoscopy, ultrasound/CT, cytology and cancer staging where applicable. At 14–30 days post cystoscopy, these participants will be contacted to collect information of any treated incidences of UTI following cystoscopy. Passive follow-up data (identification of cancer diagnosis and stage) will be collected through the NCRAS at 1, 2 and 3 years after the end of the trial for all participants who have self-tested (excluding withdrawals). Summary data will also be collected through NCRAS, requested by geographic area, for a population comparable to Cohort 2.

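### Aim 2 promises the prevalence of undiagnosed diabetes, but HbA1c is taken only from glycosuria-positive clinic attenders, so the design can give a detection yield and not a prevalence

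*Protocol article*

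**What the plan says.** Under Study aims and objectives, Aim 2 lists among the targets of Cohort 2 the "prevalence of glycosuria and undiagnosed diabetes within a high-risk community-based population".

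Investigation of glycosuria then sets out who is examined. "Participants randomised to the glycosuria arm of Cohort 2 will be investigated for the presence of glycosuria". The clinic invitation is triggered by one positive strip: "If a single positive result is identified on research nurse review of the glucose test parameter". The blood test is done there: "At the clinic, participants will undergo hemoglobin A1c (HbA1c) blood testing". For the others in that arm, "Participants in the glucosuria testing arm without glycosuria will receive a letter confirming their normal result", with advice to see the GP if symptoms develop. No blood test is described for them.

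In the haematuria arm the clinic tests are different: "At this clinic, participants will undergo a urinary tract ultrasound scan (USS) and provide a urine sample for cytology".

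Primary outcome 6 reads: "Glycosuria clinic outcomes will be measured via the proportions of those with an elevated HbA1c following collection of a blood sample". Under Data collection, "Passive follow-up data (identification of cancer diagnosis and stage) will be collected through the NCRAS". The same section says that the questionnaire asks about diabetes diagnosis and management. Known diabetes is not among the Cohort 2 exclusion criteria.

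**The concern.** A prevalence of undiagnosed diabetes counts every man with the condition who does not know it, whether or not his strip was positive. The design observes HbA1c in strip-positive attenders of one arm and in nobody else. Bladder cancer, also named in Aim 2, is treated differently: all self-testers are to be followed through the cancer registry at 1, 2 and 3 years, so cancers in strip-negative men have a route into the data. Diabetes has no such route.

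An analysis plan cannot repair this. The missing quantity is the number of strip-negative men with diabetes, and no described data source holds it. A correction would need a strip sensitivity from outside the trial, and the result would then be a modelled figure and not an observed one. What is at stake is whether the trial can report on one of its stated aims, and whether a yield or a predictive value is later taken for a prevalence.

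**Working it through.** The document gives no figure for diabetes prevalence, strip accuracy or clinic attendance, so there is no stated result to reproduce. The check is what can be estimated from the data described.

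**Inputs from the document**
- Cohort 2 is expected to randomise 1200 men (Sample size(s)) in approximately equal arms (Randomisation): 1200 / 2 = about 600 in the glycosuria arm.
- HbA1c source: strip-positive glycosuria-arm attenders only.
- Strip-negative men and haematuria-arm men: no HbA1c, and no diabetes follow-up.

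**Assumptions, not in the document**
- True prevalence of undiagnosed diabetes p: 3% to 8%.
- Sensitivity Se of at least one positive strip: 20% to 100%.
- Strip specificity Sp: 95% to 99%.
- Clinic attendance A: 80% or 100%, equal for true and false positives.
- In steps 1 to 3, known diabetes is removed, raised HbA1c is taken to mean diabetes, and all 600 men are treated as free of known diabetes for simplicity.

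**Formulas**
- Yield per man tested: Y = p × Se × A, so p = Y / (Se × A).
- Outcome 6: p·Se / [p·Se + (1 − p)(1 − Sp)]. Attendance cancels.

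**Step 1. One observed yield, many prevalences.** Suppose 12 of 600 men are found: Y = 2.0%, Wilson 95% CI 1.1% to 3.5%.

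| Se | implied p, A = 100% | implied p, A = 80% |
|---|---|---|
| 100% | 2.0% | 2.5% |
| 80% | 2.5% | 3.1% |
| 60% | 3.3% | 4.2% |
| 40% | 5.0% | 6.25% |
| 20% | 10.0% | 12.5% |

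The confidence interval covers sampling error in the yield. It says nothing about which row applies.

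**Step 2. One prevalence, many yields.** Take p = 5%, so 600 × 0.05 = 30 men, with full attendance. Se of 20, 40, 60 or 80% finds 6, 12, 18 or 24 men, and the yield is 1.0, 2.0, 3.0 or 4.0%. At Se = 40%, 18 of the 30 are missed. With 80% attendance, 30 × 0.4 × 0.8 = 9.6 are found and 20.4 missed.

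**Step 3. Outcome 6 is a different quantity.** At p = 5% and Sp = 98%, it is about 34% (Se = 20%) to 61% (Se = 60%). At Sp = 95% the same range of Se gives 17% to 39%, and at Sp = 99% it gives 51% to 76%. Letting p vary as well:
- p = 3%, Se = 20%, Sp = 95%: 0.006 / (0.006 + 0.0485) = 11%.
- p = 8%, Se = 60%, Sp = 99%: 0.048 / (0.048 + 0.0092) = 84%.

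It behaves as a predictive value, driven largely by specificity.

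**Step 4. Known diabetes can reverse the direction.** Return to p = 5%, Se = 40%, full attendance: 12 undiagnosed men found. If K men with known diabetes also test positive, attend and have raised HbA1c, the raw figure per man in the arm is (12 + K) / 600. It equals 5% when K = 18. A smaller K puts it below the true 5%, and a larger K above. The document gives no basis for K.

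**The case against.** The fair case on the other side is that this is one phrase in an aims sentence. The outcomes themselves are properly described. Outcome 4 uses the word prevalence for glycosuria only, which can be estimated. Outcome 6 states its denominator, and the Statistical analysis section presents the HbA1c result among men referred to the clinic. Nothing says that either figure will be reported as diabetes prevalence. One could even read Aim 2 so that prevalence governs only glycosuria, although that is not the natural reading. Most of this stands: the fault lies in the aim and in the lack of an outcome that matches it. It does not remove the point, because the stated target still has no estimator.

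Two stronger readings are tempting and are not supported.

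- A reader might infer that the diabetes figure will mis-set the economic model and the phase III trial. The Economic evaluation section describes a model of haematuria screening for bladder cancer, and Research need says the later trial concerns bladder cancer mortality. The nearest text, an exploratory item on rates of cancers and other illnesses per arm, can be read as rates as detected. No sample size rests on diabetes prevalence.
- A reader might infer that the trial will understate prevalence by a known factor, or overstate it several-fold through outcome 6. Every input to such a multiple is assumed, and the document never presents outcome 6 as a prevalence. A fixed understatement also requires that known diabetes be removed and that raised HbA1c equal diabetes. Neither is stated, and elevated HbA1c is defined by local reference ranges.

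**Conclusion.** The point holds as a mismatch between Aim 2 and the design. The prevalence of undiagnosed diabetes cannot be estimated from the data described, and this conclusion needs none of the assumed values. The yield per man tested would equal the prevalence only if strip sensitivity and clinic attendance were both 100%, known diabetes were removed, and raised HbA1c were the same as diabetes. With the last two conditions met but not the first, the yield is a lower bound. With known diabetes left in, even the direction is open.

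The size of any error depends on strip sensitivity, attendance and the handling of known diabetes, none of which the document gives. The figures above only show how wide the uncertainty is. The consequence is limited, since diabetes is the comparison condition of the reciprocal design. The aim should still be corrected, because it determines what the trial may claim and the correction is cheap.

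**What to change.** In Aim 2, keep the prevalence of glycosuria and replace the reference to undiagnosed diabetes with *yield of raised HbA1c from glycosuria self-testing in men without known diabetes*. Define it as follows:

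- Numerator: glycosuria-arm men without self-reported diabetes who have raised HbA1c at the clinic.
- Denominator: all glycosuria-arm men without self-reported diabetes who self-tested.
- Presentation: percentage with a 95% Wilson interval, as for the other proportions.

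The numerator should be raised HbA1c and not newly diagnosed diabetes, because no described data item returns the GP's diagnosis. Report outcome 6 as a PPV-type proportion, restricted in the same way to men without known diabetes, and say that neither figure is a prevalence of diabetes.

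The data are already planned: diabetes status from the questionnaire, strip results from the app or freephone, and HbA1c from the clinic database. The questionnaire is held apart from the strip results until the end of the trial, so the restriction is applied at analysis. The cost is a change of wording, one extra denominator, reliance on self-report for known diabetes, and a less ambitious aim. Making prevalence itself estimable would need HbA1c information on strip-negative men, which is a change of design that this point does not ask for.

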## Methods and analysis

### Study design and setting

Eligibility for Cohort 1: men and women aged 55–80 years who are registered with a GP within the Leeds Clinical Commissioning Group area, who are part of the Yorkshire Lung Screening Trial^24^ and have given consent to be contacted by other research teams (figure 1).

